#### 5.4 Study follow-up and missing data

For evaluation of incidence of severe adverse events, it is expected that the coverage will be close to 100% as these are to be collected through national register linkage. Patients who withdraw consent will be censored right after withdrawal in time-to-event models. Patients who emigrate from Sweden or die before the end of 5-year follow-up will be censored at the time of emigration and date of death, respectively. All other patients not experiencing substantial adverse events during the study follow-up will be censored at the date of individual 5-year follow-up. The primary conclusions of the study will be based on analyses conducted on all randomized patients (with exception of those who withdraw their consent) under the principle of intention-to-treat.

For evaluation of non-inferiority, a sensitivity analysis will be conducted using both multiple imputation of missing body weight data, as well as last observation carried forward (LOCF) imputation. The results of these analyses will be reported together with results of the primary analysis.

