Information regarding complications is collected during visits and registered in SOReg where a number of complications are listed but where there is also a field for "other". The seriousness of the complications is assessed continuously and finally after 5 years (primary endpoint). In case of doubt, the severity of the complication is determined by a reference group, which consists of 3 experienced bariatric surgeons ([name], [name], [name]).

In the calculations for long-term complications (5 years), i.e. patients who have undergone GBP and who incur some kind of serious complication (need for surgery for complication, revision surgery, serious nutritional problems, or chronic abdominal pain), it has been shown during the course of the study that the number of substantial AE (adverse events) is significantly higher than we initially expected. This has made it possible, after renewed power calculations based on new data, to reduce the number of included patients, ie. see Statistical analysis plan v 5.

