### 112 3.4 Data collection and follow-up

113

114 Baseline data regarding demographics and health parameters will be collected by the operating  
115 clinics using standardized questionnaires and measurements. The data collection is facilitated using a  
116 central computerized system within the Scandinavian Obesity surgery Registry - SOReg.

117 Clinical health examination of the patients including data on body weight will be conducted at 6  
118 weeks, 1 year, 2 years, and 5 years after surgery.

119 Follow-up regarding substantial adverse events will be conducted using clinical information as well as  
120 by using Swedish and Norwegian national health registries (see below). These registries have, in  
121 general, a close to complete coverage. Individual patients can be monitored using the unique  
122 personal identification number assigned to every person residing in Sweden and Norway.

123 In order to analyze data for primary and secondary objectives, data retrieved from SOReg will be  
124 linked by personal identification number to the following registers: Swedish Patient Registry;  
125 Prescribed Drug Registry; Critical Care Registry, registers of Social Insurance Agency; National  
126 Diabetes Registry; and Cancer registry. The corresponding Norwegian registries will also be used.

127 Primary objectives will be evaluated after 5-years of follow-up.

Extended follow-ups of the patients beyond the 5-year study period are planned in order to evaluate long-term health effects and safety of SG vs GBP. These analyses are not covered in this analysis plan.

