## 4. Study outcomes

A list of substantial adverse events in bariatric surgery (tabl 2) was predefined before study start. Possible occurrence of any of these will be identified in the CRF (SOREg) but additionally from the national quality health care registries (listed above) during 5-years of follow-up. A superiority of SG over GBP would require >35% fewer patients experiencing one or more substantial adverse event.

Time to occurrence of first substantial adverse event will be analysed as the co-primary outcome. Patients will be defined as either having or not having an event, and thus the number of events in the same patients will not be summarized.

For non-inferiority, weight loss difference over 5-years in patients operated with SG as compared to GBP will be evaluated with regards to the non-inferiority margin of 5%.

Table 1: Primary outcomes:

| Outcome                    | Time frame                  | Explanation                                                                          |
|----------------------------|-----------------------------|--------------------------------------------------------------------------------------|
| Weight loss                | At 5 years after surgery    | Change in weight from baseline in % of total body weight                             |
| Substantial adverse events | Over 5 years after surgery. | Number of patients with any substantial adverse events defined according to table 2. |

Table 2: Substantial adverse events: (events that may have a significant and/or longstanding effect on patients' health and/or everyday life).

| Substantial adverse event              |                                                                                                                                                                                                                                                                                               |
|----------------------------------------|-----------------------------------------------------------------------------------------------------------------------------------------------------------------------------------------------------------------------------------------------------------------------------------------------|

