| Frequent and severe food-related problems | Affecting everyday living for at least 3 months (such as hypoglycemia, pain, vomiting, nausea) in accordance with the "BEST/ SOReg template" available on the website.                                                                    |
| Severe postprandial hypoglycemia          | Hypoglycemic episodes associated with loss of consciousness/seizures or requiring drug treatment                                                                                                                                          |
| Severe GERD                               | GERD symptoms that cannot be controlled with medication (e.g., volume reflux). Barrett's esophagus (with endoscopy performed within 2 years before surgery showing absence of Barrett).                                                   |
| Serious nutritional problems              | Need for enteral (using a feeding tube to the gastrointestinal tract) or total/supplemental parenteral nutrition                                                                                                                          |
| Chronic abdominal pain                    | Pain (>6 months) requiring regular (> 1 time/week) medication with opioids (ATC code N02A, including tramadol and codeine) and/ or abdominal pain significantly affecting daily life (prohibiting normal work, leisure activities, etc.). |
| Substantial micronutrient deficiencies    | Clinically relevant, symptomatic, vitamin and/or mineral deficiencies                                                                                                                                                                     |
| Severe anemia                             | Hemoglobin <100 g/L in women and <110 g/L in men.                                                                                                                                                                                         |
| Other serious complication                | Not pre-defined but, based on clinical data combined with national registry data, deemed to be a serious adverse event related to the surgery. If need be, these events can be assessed by a reference group.                             |

148

149 Secondary outcomes:

| Outcome                                      | Time frame                  | Explanation                                                                                                                 |

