## Appendix:

The unforeseen global Covid-19 pandemic resulted in that almost all elective benign surgery in Scandinavia was cancelled from March 2020. Thus, the pandemic had severe consequences on the recruitment to the BEST trial during 2020-2021.

During autumn of 2021 the BEST steering committee decided to perform an additional analysis of the power for primary endpoints.

Additional information (Courcoulas et al, JAMA Surg 2020 March; Howard et al, JAMA Surg 2021 Dec) revealed that the risk of any of the predefined substantial adverse events after bariatric surgery is higher than previously anticipated in the revised power calculation, i.e. >25% instead of 13%. These figures were confirmed in an analysis of real-world data from the bariatric national quality register SOReg in Sweden which registered all patients undergoing sleeve or bypass in Sweden since 2007.

An independent statistician performed the analysis based on information above, but also on 2-year data in BEST. In conclusion, it was stated:

Two post hoc power analyses were conducted based on the data from February 2022:

*1. Weight reduction. In the protocol the following is stated "This sample size will also have >95% power to evaluate non-inferiority of 5% weight loss difference over 5 years between the two groups, assuming 15 kg standard deviation in weight loss over follow-up with two-sided 2.5% significance level.". The post hoc power calculation is based on the two-year follow up data where an average weight loss for all patients (both groups, N=1031) of 29.3 kg was attained with a Sd=21.6. Given a loss to follow up of 20% from 2 year follow up to the 5-year follow up the sample size is assumed to be  $(1031 \cdot 0.80)/2 = 413$  patients per group. With a non-inferiority level of 5 kg weight loss the power is found to be 90% if  $n=393$  per group, and 95% if  $n=486$  per group (<https://www.sealedenvelope.com/power/continuous-noninferior/>).*

*2. Substantial adverse events. This post hoc power calculation is for a superiority test where the rate is assumed to be 25% for the gastric bypass at 5 years and sleeve would have a 35% lower level, i.e.  $25\% \cdot 0.65 = 16.25\%$ . Given a sample of  $n=413$  per group the post hoc power will then be 87.5%.*

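### Near-complete register coverage is claimed for all substantial adverse events, but several components depend on clinic visits; patients who miss later visits stay event-free to 5 years, and no sensitivity analysis tests this

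*Combined protocol and SAP*

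**What the plan says.** **Coverage.** SAP version 5, section 5.4, on the incidence of adverse events: "it is expected that the coverage will be close to 100% as these are to be collected through national register linkage".

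**Censoring.** The same section censors at consent withdrawal, emigration and death, and then: "All other patients not experiencing substantial adverse events during the study follow-up will be censored at the date of individual 5-year follow-up". Loss to clinic follow-up is not a censoring reason. The missing-data sensitivity analyses named there (multiple imputation and LOCF) concern body weight only.

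**Sources of events.** Three other places describe a mixed source:
- Protocol, Primary outcome measure: "Information regarding complications is collected during visits and registered in SOReg".
- SAP section 3.4: "Follow-up regarding substantial adverse events will be conducted using clinical information as well as" the national registries.
- SAP section 4: "Possible occurrence of any of these will be identified in the CRF (SOREg) but additionally from the national quality health care registries".

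**Registers.** Section 3.4 says that SOReg data will be "linked by personal identification number to the following registers: Swedish Patient Registry", then the prescribed drug, critical care, social insurance, diabetes and cancer registers, and the Norwegian counterparts.

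**Visits.** Section 3.4 schedules them at 6 weeks and at 1, 2 and 5 years.

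**Expected loss.** SAP Appendix, item 1: "Given a loss to follow up of 20% from 2 year follow up to the 5-year follow up". Item 2 uses the reduced number for the adverse-event power.

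**The concern.** The coverage sentence gives one reason, register linkage, for a composite with more than one source. Where a component is defined by symptoms or a laboratory value, a missed visit may mean that nobody could record it. The censoring rule then treats the absence of a record as the absence of an event.

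The gap is longest late in follow-up. No visit is scheduled between years 2 and 5, so a patient who misses the 5-year visit has three years without planned ascertainment of these components.

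This is a co-primary outcome in a trial where every patient is told which operation was done. If events go unrecorded equally in both arms, absolute risks are too low and some power is lost. If attendance differs by arm, part of the observed hazard ratio reflects attendance. As the SAP stands, a reader of the results could not tell how much.

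**Working it through.** **1. Table 2 components set against the named registers**

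| Component | Likely source |
|---|---|
| Death, ICU admission, intervention under general anesthesia, revision surgery, in-hospital care | Registers, plus SOReg |
| Regular opioid use for abdominal pain; drug-treated hypoglycemia | Drug register at least in part |
| Food-related problems for 3 months or more | Clinic, by a BEST/SOReg template |
| GERD symptoms not controlled by medication | Clinic |
| Pain limiting daily life, without opioids | Clinic; work incapacity perhaps in social insurance data |
| Hemoglobin thresholds | Laboratory value; not among the mandatory tests in the protocol (Secondary outcome measures) |
| "Clinically relevant, symptomatic, vitamin and/or mineral deficiencies" | Clinic; partly coded in the patient register |
| Barrett's esophagus | Endoscopy; may be coded in the patient register |

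The right-hand column is inferred from the definitions and the register list. The SAP has no such table. None of the registers named in section 3.4 is described as holding symptoms or laboratory values.

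**2. The plan's own figure**

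The coverage expectation has no inputs and cannot be recomputed. The nearest figure is Appendix item 2: 87.5% power with 413 per group and 25% vs 16.25%.
- n = 1031 × 0.80 / 2 = 412.4, stated as 413.
- Two-proportion power at two-sided 5% is 87.6%, so the figure reproduces. (At the plan's two-sided 2.5% it is 80.8%; that is a separate matter.)

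The 413 is what remains after the assumed visit loss. If adverse-event coverage were close to 100% whatever the attendance, about 1752 / 2 = 876 per arm would contribute. The Appendix thus treats the adverse-event outcome as dependent on visits, and section 5.4 does not.

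**3. Share of events missed**

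Assumptions, none given by the documents except the 20%:
- s, the share of first events that are visit-dependent: 20–50%.
- m, the share of patients absent at year 5: 20% (the Appendix figure for years 2 to 5) or 35% (illustrative).
- Absent patients attended to year 2, and events are uniform over 5 years, so 3/5 of their visit-dependent events fall in the unobserved period.

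Missed share = s × m × 3/5.

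| | s = 20% | s = 50% |
|---|---|---|
| m = 20% | 0.20 × 0.20 × 0.6 = 2.4% | 0.50 × 0.20 × 0.6 = 6.0% |
| m = 35% | 0.20 × 0.35 × 0.6 = 4.2% | 0.50 × 0.35 × 0.6 = 10.5% |

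Earlier drop-out, or missing hemoglobin among attenders, would raise these shares. A later register event in the same patient would lower them.

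**4. Equal attendance**

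Both risks are multiplied by the same factor, so the risk ratio is unchanged. With 876 per arm at two-sided 2.5% (two-proportion approximation):
- True 25% vs 16.25%: power 98.9% with full capture. With 10.5% missed, observed risks are 22.4% vs 14.5% and power is 97.7%.
- True 13% vs 8.45% (SAP section 5.1): power 79.9% with full capture, 78.7% with 2.4% missed and 74.3% with 10.5% missed.

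**5. Unequal attendance (illustration only)**

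Non-attendance 35% in GBP and 45% in SG, no true difference:
- s = 20%: (1 − 0.20 × 0.45 × 0.6) / (1 − 0.20 × 0.35 × 0.6) = 0.946 / 0.958 = 0.987.
- s = 50%: 0.865 / 0.895 = 0.966.

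At 25% true risk and 876 per arm, the chance of a significant result for SG is 1.8% and 3.1%, against a nominal 1.25% in that direction. With the arms exchanged, the ratios are 1.013 and 1.035, against SG.

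**The case against.** **The registers may hold more than the definitions suggest.** They cover inpatient and specialist outpatient diagnoses, dispensed drugs and social insurance. Anemia leading to care, coded deficiencies, Barrett's esophagus and pain preventing work may be found there. The protocol also refers to other relevant national registers and leaves linkage variables and data handling to separate plans that are not part of these documents. This stands. A reader might infer that the components exist only in visit data; the documents do not show that. They support likely incomplete capture, and section 5.4 gives no basis for assuming otherwise.

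**Patients absent at year 5 were not necessarily unseen before.** There are three earlier visits, and complications are assessed continuously. This also stands. Giving such patients no visit-based capture at all would yield 7% to 17.5% missed at 35% non-attendance (0.20 × 0.35 to 0.50 × 0.35), which is too high.

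**Attendance is not documented.** The 20% is a planning assumption for one interval, made in the weight calculation. The 1031 patients with 2-year data must not be divided by 1752, because patients operated on after about February 2020 had not reached 2 years in February 2022.

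**Nothing shows unequal attendance.** A reader might infer a spurious advantage for SG. The documents give no attendance by arm, and the bias could go either way. Its illustrated size is small beside the planned 35% reduction.

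**The censoring date is open to interpretation.** The individual 5-year follow-up date is undefined for a patient without that visit. Reading it as the 5-year date is natural but not certain.

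The objection limits the size of the problem. It does not reconcile the coverage sentence with the sources named in the protocol and in SAP sections 3.4 and 4.

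**Conclusion.** The point holds in a limited form. Register linkage cannot be assumed to give near-complete coverage of every Table 2 component. The censoring rule turns possible non-observation into event-free time, and no sensitivity analysis tests the consequence for this co-primary outcome.

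Under the assumptions in the working, 2.4–6% of events are missed at 20% year-5 non-attendance and 4.2–10.5% at 35%. With equal attendance, this means lower incidence estimates and a power loss of at most about 1 percentage point at the 25% rate, or about 6 points at the 13% rate. With unequal attendance the hazard ratio is biased, by an amount and in a direction that the documents cannot settle.

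It would go too far to conclude that the primary analysis is invalid, or that the full composite should be censored at the last attended visit. That change would either discard known register events after that visit or, if those were kept, make censoring depend on outcome. At 35% non-attendance it could also remove up to 0.35 × 3/5 = 21% of planned follow-up time.

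**What to change.** In SAP version 5:

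1. **Section 5.4, coverage.** Limit the near-100% statement to register-ascertained components, and say that the others depend on visit attendance. State which date applies to a patient with no 5-year visit.
2. **Table 2.** Add a source column: register, visit or laboratory, or both.
3. **Primary analysis.** Keep the full composite and its present censoring rule. Add a required sensitivity analysis of the register-ascertained composite, censored at 5 years, emigration or death, with the existing handling of withdrawn consent.
4. **Visit-dependent components.** Analyse them separately as a sensitivity analysis, with follow-up ending at the last clinic ascertainment, or by interval-censored or multiple-imputation methods.
5. **Reporting.** Tabulate attendance at 1, 2 and 5 years, and hemoglobin availability, by arm.

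The cost is classifying the components, a few extra models and tables, and a less favourable statement about coverage. No new data collection is needed, and the primary analysis does not change.

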## 3. Study Design

### 3.1 Overview

This is a randomized, Scandinavian multi-centre study comparing the two most abundant bariatric surgery techniques worldwide; laparoscopic gastric bypass (GBP) and laparoscopic sleeve gastrectomy (SG). Study design is parallel group study with 1:1 allocation between GBP and SG.

To be invited to participate in the study as a collaborating centre, the operating bariatric clinic has to perform at least 100 bariatric surgeries annually, report to the Scandinavian Obesity Surgery Registry (SOREg) and be able to meet all criteria set in the project plan. The study, to be conducted at approximately 20 bariatric surgery clinics in Sweden and Norway, will include 2100 obese patients approved for bariatric surgery (1050 patients to be operated with SG and 1050 with GBP).

89 The follow-up time for the primary objectives is 5-years.

90

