### 105 3.3 Eligibility criteria

106

107 The target group is adult (>18 years) patients with severe obesity (BMI 35-50 kg/m^2) eligible and  
108 approved for bariatric surgery in Sweden or Norway. To be included in the study, patients need to  
109 fulfil the inclusion criteria, not having any exclusion criteria, and be eligible for operation using both  
110 surgical techniques. Detailed inclusion and exclusion criteria are provided in the study protocol.

111

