| Death                                  | Death associated with bariatric surgery.                                                                                                                                                                                                                                                      |
| Intervention under general anesthesia  | Complication according to Clavien-Dindo 3b or higher associated with the bariatric intervention (excluding gallstone interventions, preexisting hernia at bariatric surgery, and plastic surgery for removal of excess skin). A sub analysis of negative diagnostic laparoscopies is planned. |
| Admission to intensive care unit (ICU) | Admission to ICU due to complications from bariatric surgery.                                                                                                                                                                                                                                 |
| Revision surgery                       | Change of surgical method; reversal or significant change of the original method. Revision surgery will be performed according to clinical practice. The indication for revision surgery (e.g. unsatisfactory weight loss or gastro-esophageal reflux) should be                              |

|                                           |                                                                                                                                                                                                                                           |
|-------------------------------------------|-------------------------------------------------------------------------------------------------------------------------------------------------------------------------------------------------------------------------------------------|
|                                           | documented.                                                                                                                                                                                                                               |
| In-hospital care                          | Due to complications related to the surgery (excluding observation without diagnosis for less than 24 hours)                                                                                                                              |

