### 5.2 Principles of analysis

171

172 The primary conclusions from this study will be based on analyses conducted under the principle of  
 173 intention-to-treat. Thus, all randomised patients, with exception to those who withdraw their  
 174 consent, will be included in the analyses. In the analysis, it is further assumed that all randomised  
 175 patients receive the treatment they were randomised to.

Those patients who are randomised but withdraw their consent to use their data will not be included in any analyses. Only the information that they were enrolled into the study and withdrew their consent, and the original treatment group to which they were allocated, will be reported.

Data from all operating clinics (centres) will be pooled in primary analyses. The study will be conducted under a common protocol for each participating clinic with the intention to pool the data for analyses.

In addition to the primary analysis using intention-to-treat population, exploratory analyses using per-protocol (as treated) populations will be conducted for all outcome variables.

For primary outcomes, two-sided 2.5% significance level will be used to identify statistically significant results. The corresponding confidence intervals to be reported will be 97.5% confidence intervals. The use of 2.5% significance is due to two primary endpoints.

There will not be any formal interim analyses on primary outcomes. The safety and Data Monitoring Committee has a responsibility to monitor adverse events and complications during the study follow-up period.

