### 5.3 Statistical analyses

Summary tables (descriptive statistics and frequency tables) will be provided for all baseline variables, outcome variables, and safety variables, as appropriate. Continuous variables will be summarized with descriptive statistics (n, mean, standard deviation, range, and median). Frequency counts and percentage of subjects within each category will be provided for categorical data.

Incidence of substantial adverse events will be analysed with time-to-event models. Time to first substantial adverse event (as defined in chapter 4 Study outcomes) from primary surgery will be recorded. Kaplan-Meier estimates of cumulative incidence of adverse events will be calculated in both treatment groups. Treatment effect will be calculated as a hazard ratio, together with corresponding confidence interval and p-value for the test of equal hazard ratio, from Cox proportional hazard regression model. The proportionality assumption of the Cox models will be evaluated graphically using "log-log" plots.

The primary conclusions will be based on a model which includes study centre as a covariate together with indicator for treatment. Explorative analyses will be conducted using sex, age, body mass index, smoking and diabetes at baseline as covariates.

For non-inferiority, the difference in weight loss between treatment groups and its confidence interval will be calculated and evaluated against the non-inferiority margin of 5%. The weight loss difference at 5-year follow-up will be estimated with a multilevel mixed-effect regression models utilizing body weight measurements at all available time points. This model takes into account the repeated measurements nested within persons over time. All randomized patients except those who have withdrawn their consent will be included in this analysis, independent of availability of body weight data during the follow-up. The primary conclusions will be based on a model which includes study center in addition to indicator for treatment.

For secondary outcomes, incidence of comorbidities during the follow-up will be evaluated with time-to-event models, and for continuous variables mixed-effect regression models will be used to evaluate differences between the treatment groups.

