Taking information above into account and in the interest of not prolonging inclusion period unnecessarily the trial steering committee took a decision to stop inclusion in BEST during spring 2022 (final date 31st of March). At termination of inclusion the number of participants that had been included and operated in BEST were 1752. The trial DSMC reviewed and supported the decision before termination of recruitment to the BEST trial.

1

2

3 Statistical analysis plan for:

4

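### The co-primary time-to-event analysis needs three small corrections: emigration from Norway, surgery-related death, and patients randomised but not operated

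*Combined protocol and SAP*

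**What the plan says.** All references are to the main SAP (version 5) unless stated.

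- **Emigration and death.** Section 5.4: "Patients who emigrate from Sweden or die before the end of 5-year follow-up will be censored", at the date of emigration or death respectively. Everyone else comes under a residual rule: "All other patients not experiencing substantial adverse events during the study follow-up will be censored at the date of individual 5-year follow-up".
- **Countries.** Section 3.1 describes a study "conducted at approximately 20 bariatric surgery clinics in Sweden and Norway". Section 3.3 takes patients "approved for bariatric surgery in Sweden or Norway". The protocol's Schedule puts the start of Norwegian inclusion in autumn 2018.
- **Death as an event.** Section 4, Table 2, lists "Death associated with bariatric surgery" as a substantial adverse event. The protocol's list under Primary outcome measure agrees.
- **Time origin.** Section 5.3: "Time to first substantial adverse event (as defined in chapter 4 Study outcomes) from primary surgery will be recorded".
- **Analysis set.** Section 5.2 includes "all randomised patients, with exception to those who withdraw their" consent, under intention-to-treat, and assumes that everyone received the allocated operation. Section 5.4 repeats the population.
- **Final count.** Appendix: "the number of participants that had been included and operated in BEST were 1752". No number randomised is given, overall or by arm.

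**The concern.** A programmer following these sections meets three patients for whom the text gives a wrong answer, an ambiguous answer or none.

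(a) An event-free patient who leaves Norway is not covered by the emigration rule and falls under the residual rule. That patient counts as observed and event-free to 5 years although the registers no longer see events.

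(b) For a patient whose first substantial adverse event is a surgery-related death, section 5.4 read alone says censor and Table 2 says event, on the same date.

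(c) A patient who is randomised, not operated, and has not withdrawn consent belongs to the analysis set but has no time zero. The protocol (Randomization) allows the allocation to be disclosed up to 24 hours before anaesthesia, so the allocation can be known before surgery.

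At stake are the risk set and event count of the co-primary safety outcome. For (c), the comparison also has to stay between the groups as randomised.

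**Working it through.** **1. The plan's own figure.** No figure in the documents depends on these rules. For context, section 5.1 assumes 13% with GBP and a 35% lower risk with SG (0.13 × 0.65 = 8.45%), with 1050 per arm at two-sided 2.5%. The implied HR is ln(1 − 0.0845)/ln(1 − 0.13) = 0.634, with 1050 × (0.13 + 0.0845) = 225 events. Schoenfeld power is Φ(√(225/4) × |ln 0.634| − 2.241) = 88.1%, close to the stated >90%.

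**2. Base cases.** I take 1752 patients (Appendix) and assume an equal split, 876 per arm. HR = ln(1 − r_SG)/ln(1 − r_GBP).
- Appendix rates, 25% and 16.25%: HR 0.616, with 876 × 0.4125 = 361 events.
- Section 5.1 rates, 13% and 8.45%: HR 0.634, with 876 × 0.2145 = 188 events.

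**3. Assumptions.** The documents give no counts, so the ranges below are assumptions.
- *Norway:* 10–30% of patients, of whom 1–5% emigrate evenly over 5 years, so on average half of each emigrant's follow-up is unseen. Emigrants: 1752 × 0.10 × 0.01 = 2 to 1752 × 0.30 × 0.05 = 26. Unseen events: 188 × 0.10 × 0.01 × 0.5 = 0.1 to 361 × 0.30 × 0.05 × 0.5 = 2.7.
- *Death:* 1–5 surgery-related deaths with no earlier Table 2 event are censored, so the affected arm's rate falls by k/876.
- *Not operated:* a fraction f of 0.5–5% of an arm (about 4 to 44 of 876) is kept and event-free, so the arm's rate becomes r(1 − f).

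**4. Results (HR).**

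| Assumed situation | Base 0.616 | Base 0.634 |
|---|---|---|
| Norway, largest case, both arms alike | 0.617 | 0.634 |
| 1 / 5 deaths censored, GBP only | 0.620 / 0.633 | 0.640 / 0.665 |
| 1 / 5 deaths censored, SG only | 0.612 / 0.593 | 0.625 / 0.589 |
| 0.5% / 5% not operated, both arms | 0.617 / 0.618 | 0.634 / 0.635 |
| 0.5% / 5% not operated, SG only | 0.613 / 0.583 | 0.631 / 0.601 |
| 0.5% / 5% not operated, GBP only | 0.620 / 0.654 | 0.637 / 0.670 |

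Unrounded, the Norwegian case moves the HR from 0.6164 to 0.6167, or from 0.6339 to 0.6341.

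**5. If non-operated patients were left out instead.** Dropping 5% from both arms lowers Schoenfeld power at two-sided 2.5% from 81.1% to 78.9% (13% rate), or from 99.1% to 98.7% (25% rate). The loss of power is minor; the reason to settle the rule is possible imbalance between arms.

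**The case against.** **Death.** The defence is strongest here. The residual rule speaks of all other patients without an event, which suggests that the groups named before it are event-free too. Section 5.3 takes its event definition from section 4, where surgery-related death is listed. Read literally, the rule would also censor at death someone who had already had an event, which makes no sense for time to first event. This largely stands as a reading of intent. A reader might infer that every surgery-related death is scored as no event. The documents do not support that: a death that follows intensive care, reoperation or hospital care already has an earlier Table 2 event. What remains is that the sentence on deaths lacks the qualifier, and a co-primary safety outcome should not rest on inference.

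**Not operated.** A reader might infer that the intention-to-treat analysis is really an analysis of operated patients. The SAP never says that such patients are dropped; it leaves their time origin undefined. Nor does the Appendix count show that a group was lost: the perioperative SAP (section 3.1) gives the same 1752 as patients included, without mentioning operation. The protocol also has a safeguard, since willingness is confirmed before randomisation, normally on the morning of surgery. The risk it names is withdrawal from the study, and sections 5.2 and 5.4 have rules for consent withdrawal. The gap concerns patients who keep their consent. It is also fair to say that patients never operated can hardly have surgical complications, so keeping them dilutes the contrast slightly.

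**Norway.** The omission conflicts with the two-country design. It does not contradict the endpoint definition or intention-to-treat. Section 3.4 also draws on clinical information and Norwegian registries, but neither can be relied on to capture events after a patient has left.

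**Conclusion.** The point holds as a specification defect in three places. The Norwegian omission and the missing time origin are plain from the text. The rule on deaths is probably meant correctly but is written without the exception it needs.

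The effect on the hazard ratio is probably small. Under the assumed ranges the Norwegian gap is negligible if emigration is alike in both arms. The other two matter only if unbalanced: across both, the HR could lie between 0.583 and 0.654 around 0.616, or between 0.589 and 0.670 around 0.634, with all affected patients in one arm. These bounds rest on assumed counts, equal arms and proportional hazards. The documents give no number of Norwegian emigrants, surgery-related deaths or patients not operated, so no estimate of actual bias can be made, and no figure stated in the plan changes.

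**What to change.** Amend sections 5.3 and 5.4 before the five-year data are analysed:

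1. **Emigration.** Censor patients who emigrate from Sweden or Norway, and name the source of the dates. The protocol (Secondary outcome measures) lists the Swedish Tax Agency and Statistisk Sentralbyrå but does not say that they supply emigration dates, so this needs confirming.
2. **Death.** State that a death meeting Table 2 is an event at the date of death, and that only other deaths are censored.
3. **Time origin.** Start the clock at randomisation, normally the day of surgery and at most about a day earlier. Keep patients who were not operated in the intention-to-treat set with register follow-up, and report the number randomised per arm beside the 1752 operated.

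**Cost.** Items 1 and 2 are mainly wording. Item 3 takes some work: section 3.4 builds the linkage from SOReg data, while the early envelopes and the separate Norwegian programme (protocol, Randomization) lie outside the SOReg module. Non-operated patients must therefore be found in all three sets of randomisation records and added to the linkage file. They add time with little risk of surgical complications, a slight dilution that intention-to-treat implies.
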